### Intervention protocol

The 12-week TE program will be performed and supported by the USTEP platform, with each patient taking part in three training sessions per week with a 60 min duration period per training session. There will be personalized training sessions: (i) warm-up and warm-down (5 min each) with mobility and proprioception exercises and respiratory exercises, (ii) aerobic exercise (30 min) with continuous outdoor walking and/or home-based with intensity on 90%–120% of HR_peak_ calculation according to HR_peak_ during 6MWT and self-reported feeling of dyspnea and leg fatigue (all participants of the tele-exercise program will use wearable-based tracking to record the covered distance and assess the cardio-oxygenation), and (iii) multijoint strength exercises (20 min) to improve the strength of upper and lower limbs on 70%–80% intensity calculation according to kilograms and repetitions (combined of HR_peak_) (this will include handgrip strength test and 30 s sit-to-stand). All tele-exercise program participants will use wearable-based tracking to assess the cardio-oxygenation. Adherence to the tele-exercise program will be recorded through wearable-based tracking, and the dedication rate will be recorded through Google Analytics, which is linked to the USTEP platform.

### Statistical analysis

For the sample size calculation of this study, a power of 85% and a confidence interval of 95% were adopted (G*Power software 3.1), with an estimated type 1 error value of 5%, given the lack of previous studies investigating the effects of a tele-exercise program in patients with OSA. We determined a sample size of 20 patients for each group. The Kolmogorov–Smirnov test will be used to assess data normality for continuous variables. ANOVA analysis of variance will be applied to compare the groups before and after the intervention period. Relationships between continuous variables will be assessed via Spearman's rho and Pearson's R correlation coefficients for non-parametric and parametric variables, respectively. Differences between cutoff strata will be assessed via the independent samples *t*-test or Mann–Whitney *U*-test where appropriate. Analysis of fNIRS data will be based on a boxcar general linear model and a custom MATLAB (MathWorks, Natick, MA, USA) script (44). A *p*-value of <0.05 will be considered statistically significant for all tests. The IBM SPSS 21 statistical package (SPSS Inc., Chicago, IL, USA) will be used for all statistical analyses.

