### Study population

This study will include newly diagnosed patients with OSA, and participants will be recruited from the Sleep Apnea Outpatient Clinics and Sleep–Wake Outpatient Clinics of the Nicosia General Hospital. We will perform a screening cognitive test via the Montreal cognitive assessment (MoCA) questionnaire to identify individuals with cognitive impairment (CI). Patients with OSA and CI will be randomized into two groups: The OSA group with CI who will undergo the tele-exercise program (TE) (Group A) and the OSA group with CI who will not undergo the TE (Group B). A third matched group (Group C) of OSA patients without cognitive impairment will act as a second control group. Group A will perform a tele-exercise program on the Unique Safe Tele-Exercise Project platform (https://ustep.gr), for 12 weeks. All patients who will be enrolled in our study will not receive continuous positive airway pressure (non-CPAP) treatment (delayed therapy) (Graphical Abstract).

The inclusion criteria for this study will be the following: age ≥18 to ≤70 years, apnea–hypopnea index (AHI) ≥15 events/h, no contraindications (e.g., unstable angina during the previous month, myocardial infarction in the previous month, resting heart rate >120 bpm, systolic blood pressure >180 mmHg, and diastolic blood pressure >100 mmHg) for the 6 min walk test (6MWT) (19, 20), body mass index (BMI) <40 kg/m^2^, no daily physical workload, no active self-reported symptoms (fatigue and dyspnea) (21, 22, 23), and pregnancy. Patients with pre-existing musculoskeletal disability were excluded because their condition may affect maximal exercise capacity (24). All participants should be able to read and understand Greek.

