
Study-related outcomes include the following. (a) *PSG study outcome*: for this aim, we will compare several sleep/wake questionnaires, and various polysomnographic quantitative and qualitative parameters at baseline and 12-week follow-up will be assessed, e.g., change in sleep architecture, sleep staging features, and respiratory features in PSG between baseline and 12-week follow-up. (b) *Questionnaire*s *on the cognitive outcome*: (i) verbal episodic memory based on subdomains of the encoding process and immediate recall, free and cued recall, and recognition and delayed recall; (ii) score in a serial verbal learning task, with control of encoding and recall, according to the modified procedure of Grober and Buschke (43); and (iii) working memory with subdomains the auditory information processing speed, flexibility, and working memory span. (c) *CPET parameters outcome*: to investigate the extent to which tele-exercise improves cardiopulmonary metabolic parameters in patients with OSA at baseline and 12-week follow-up in participants with non-CPAP treatment. (d) *fNIRS outcomes*: cerebral oxygenation according to fNIRS-based measure levels of oxyhemoglobin (HbO) and deoxygenated hemoglobin (deoxy-Hb). For this aim, we will compare cerebral oxygenation values fNIRS at baseline and following a 12-week follow-up in the abovementioned three groups of patients.

All the above assessments will be performed at baseline and 12-week follow-up.

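### The only stated test of the study groups is an ANOVA that, as worded, takes in the non-randomised Group C, so a significant three-group result cannot by itself be attributed to tele-exercise

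*Protocol article*

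**What the plan says.** Under Study population, the article confines randomisation to the impaired patients: "Patients with OSA and CI will be randomized into two groups". These are A (tele-exercise) and B (none). It then adds: "A third matched group (Group C) of OSA patients without cognitive impairment will act as a second control group". The Assessment section gives MoCA the task of sorting participants into groups, and the Abstract confirms that C does not exercise.

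The aim, at the end of the Background, is the effect of the 12-week program on cognition and on brain oxygenation and metabolism. The group test in Statistical analysis is: "ANOVA analysis of variance will be applied to compare the groups before and after the intervention period". For fNIRS, the outcome text under Assessment names all three groups; it will "compare cerebral oxygenation values fNIRS at baseline and following a 12-week follow-up in the abovementioned three groups of patients". The t-test and Mann-Whitney sentence concerns strata formed by cut-offs and is not tied to A versus B. The size is fixed at 20 per group, and p<0.05 counts as significant for every test.

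**The concern.** A and B differ only by chance and by the program, so A versus B answers the trial's question. C differs from A in two respects at once, cognitive impairment and exercise, and from B in impairment. Matching cannot remove that difference, because cognition defines the group.

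A three-group F test asks whether any of the three means differ. If C alone stands apart, the test is significant with A equal to B. On a change score for MoCA there is a second route. A and B were picked for low scores and C for high ones, so on retest A and B tend to drift up and C down. That drift makes A look improved relative to C, which is the direction of the hypothesis in the Abstract. At stake is reading such a result as a benefit of tele-exercise.

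**Working it through.** **Inputs from the article.** Three groups of 20 (N = 60), α = 0.05, power 85%; A and B randomised, C selected by MoCA.

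**Assumptions, not in the article.** MoCA mean 24-26, SD 3, reliability 0.7-0.9, cut-off 26; a gap of 0.5-1.0 SD between C and A/B on other outcomes.

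**The plan's own figure.** "We determined a sample size of 20 patients for each group" cannot be reproduced, because the article gives no effect size or outcome for it. Solving backwards at 85% power, n = 20 corresponds to f = 0.44 for a three-group ANOVA, or d = 0.97 for a two-sided A-versus-B t-test. The point here uses n = 20 only as an input.

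**Reading 1: ANOVA at week 12.** Let A = B and let C be higher by D SDs.
- The means (0, 0, D) have variance 2D²/9, so f = D√2/3.
- The noncentrality is λ = N f² = 60 × 2D²/9 = 13.33 D².
- The critical value of F(2, 57) at 5% is 3.16.

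| D (SD) | f | λ | P(significant), no exercise effect |
|---|---|---|---|
| 0.5 | 0.236 | 3.33 | 0.34 |
| 0.8 | 0.377 | 8.53 | 0.72 |
| 1.0 | 0.471 | 13.33 | 0.90 |

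The same ANOVA at baseline behaves alike (0.90 at D = 1), before anyone has exercised.

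The next step simulates selection on MoCA below versus at or above 26, with no exercise effect. The week-12 three-group ANOVA on MoCA rejects in about 99% or more of trials. On the week-12 value of another cognitive test correlated 0.6 with MoCA (MoCA mean 25), it rejects in 62-88%.

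**Reading 2: group-by-time or change.**
- *Fixed gap.* It cancels. With D = 1, 1.5 or 2 and pre-post correlation 0.7, the three-group test on change rejects in 4.8-5.0%.
- *MoCA itself.* Regression to the mean remains. With the cut at the mean, each side lies on average 0.798 SD from it. The expected A-minus-C difference in change is 2 × (1 − r) × 0.798 × 3: 1.44 points at r = 0.7 and 0.48 at r = 0.9. Over the assumed range the simulated difference is 0.5-1.5 points. The three-group test on change rejects in about 19-59%, and A versus C on change in about 20-58%.
- *Other cognitive tests.* Selection on MoCA reaches their change scores only through measurement error shared at the same session. With true-score correlation 0.6, MoCA mean 25 and error correlation 0 to 0.3, rejection is about 5-8%.

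**A versus B on change.** About 5% under no exercise effect in every scenario.

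**The case against.** The strongest case on the other side is that the article does not spell out the model. Before and after may well mean a group-by-time term, contrasts may follow, and a fuller protocol or SAP may name A versus B. Under a group-by-time reading the test does carry information about exercise: with a true effect of 0.5 SD in A, a fixed gap in C and correlation 0.7, it rejects in 52% of trials, against 51% for A versus B. The regression-to-the-mean figures belong to MoCA, whereas the cognitive outcomes listed under Assessment are verbal episodic memory, serial verbal learning and working memory. The article gives no gap between C and the others on sleep, CPET or fNIRS measures, and it calls C matched. A baseline ANOVA would also make a pre-existing gap visible.

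Most of this stands, and it limits the size of the problem. It does not remove the problem. The article states a comparison of the groups, names three for fNIRS and gives no separate role to the randomised pair. An unseen contrast would not correct that wording, and under either reading C can drive the result.

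A reader might infer that the authors intend to claim efficacy from A versus C. No sentence says so. Calling C a control also fits a non-exercising, unimpaired reference group, and objecting to the word is only a preference.

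**Conclusion.** The point holds as a limit on interpretation: a significant three-group result cannot by itself be attributed to tele-exercise. Its size depends on the reading. It is severe for a week-12 comparison of cognition. It is moderate to large for change in MoCA. It is small for change in other cognitive tests, and possibly small for outcomes unrelated to cognition. All rates rest on the assumed MoCA distribution, reliability, cut-off and gaps; the logic does not.

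Two stronger readings are tempting and not supported. One is that the ANOVA says nothing about tele-exercise; a group-by-time test does respond to a true A-versus-B difference. The other is that it is bound to be significant on cognition; on change in MoCA it rejects in 19-59% of null trials, and on other cognitive tests it stays near 5-8%.

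**What to change.** In Statistical analysis, state that the tele-exercise effect is tested only by the randomised A-versus-B comparison at week 12, for example by ANCOVA of the week-12 value adjusted for the baseline value, and leave Group C out of that test. Report C as a non-randomised reference, either descriptively or in a separate B-versus-C comparison. State that no efficacy conclusion will be drawn from A versus C or from the three-group F test. Bring the fNIRS outcome text under Assessment into line.

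The cost is wording and analysis only. No patients, visits or measurements are added, and the data already planned support the A-versus-B test.

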## Abstract

Obstructive sleep apnea (OSA) is associated with a number of adverse health effects, particularly on brain health. Chronic sleep disruption caused by OSA can adversely affect cognitive health. Exercise is recommended as a non-pharmacological intervention for patients who are intolerant to continuous positive airway pressure (CPAP) and has been shown to have beneficial effects on brain health and cognitive function. This protocol aims to investigate the effects of a 12-week tele-exercise program on cognitive function and specific parameters of brain activity, including brain metabolism and oxygenation, in patients with OSA. The project aims to demonstrate the multidimensional relationship between exercise, cognition, and brain oxygenation/metabolism. Our local ethics committee has approved the study. Our population sample (Group A, OSA with cognitive impairment (CI) and tele-exercise; Group B, OSA with CI and no tele-exercise; Group C, OSA without CI and no tele-exercise) will undergo assessment both before and after a 12-week tele-exercise intervention program. This assessment will include a comprehensive battery of subjective and objective assessment tests. Data will be analyzed according to group stratification. We hypothesize a beneficial effect of tele-exercise on sleep and cognitive parameters, and we are confident that this study will raise awareness among healthcare professionals of the brain health benefits of exercise in patients with low compliance to CPAP treatment. The protocol of our manuscript entitled "The impact of a 12-week tele-exercise program on cognitive function and cerebral oxygenation in patients with OSA: Randomized Controlled Trial -Protocol Study" has been registered on ClinicalTrials.gov with ID NCT06467682.

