This protocol aims to investigate the effects of a 12-week tele-exercise program on cognitive function and specific parameters of brain activity, including brain metabolism and oxygenation, in patients with OSA. The project aims to highlight the multidimensional relationship between physical exercise, cognition, and brain oxygenation/metabolism.

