## Discussion

This study is designed to explore the impact of a 12-week tele-exercising program on the cognitive profile as well as on specific parameters of brain function and sleep architecture in OSA patients without CPAP treatment. In addition, this study aims to highlight the multidimensional relationship between physical exercise, cognition, brain oxygenation/metabolism, and sleep quality.

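### Cognition and cerebral oxygenation would be related by correlations with no age adjustment in patients aged 18 to 70, so a coefficient from levels at a visit could reflect shared ageing

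*Protocol article*

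**What the plan says.** The protocol article's Statistical analysis section gives one method for relating variables: "Relationships between continuous variables will be assessed via" Spearman's coefficient where variables are treated as non-parametric and Pearson's where they are treated as parametric. The significance limit of 0.05 applies to every test. The section names no covariate, partial correlation or regression for this purpose. The general linear model it mentions is for processing the fNIRS signal.

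Study population admits patients of "age ≥18 to ≤70 years". Group C is described as matched, but the matching factors are not named.

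The relationship itself is an aim. The Abstract says the project should "demonstrate the multidimensional relationship between exercise, cognition, and brain oxygenation/metabolism". Background repeats this, and the Discussion adds sleep: "this study aims to highlight the multidimensional relationship between physical exercise, cognition, brain oxygenation/metabolism, and sleep quality".

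On numbers, the article says: "We determined a sample size of 20 patients for each group". That gives 20 per group, 40 in A and B together, and 60 in all.

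**The concern.** A bivariate coefficient cannot hold a third variable constant. If cognitive scores and oxy- or deoxyhaemoglobin levels both vary with age, they will correlate across patients of different ages even when neither affects the other. Matching Group C, or analysing by group, does not remove this, because age still varies inside each group.

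At stake is the relationship aim. Plain correlation is the only method stated for it, and the article expects its results to inform mechanism. A significant coefficient that ageing alone could produce does not support that reading.

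**Working it through.** **The plan's own figure.** The article gives 20 per group for 85% power and 5% type 1 error, but no effect size, standard deviation or test. The figure can therefore be neither reproduced nor refuted. It is used here only as n.

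**Inputs from the article.** Unadjusted Pearson or Spearman; p < 0.05, taken as two-sided; n = 20 (one group) or 60 (all groups); ages 18 to 70.

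**Assumed input.** The article gives no correlation of age with either measure, so a range is shown: 0.3, 0.4, 0.5 and 0.6, the same for both.

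**Step 1: induced correlation.** If age is the only link, r(cognition, oxygenation) = r(age, cognition) × r(age, oxygenation). This gives 0.3² = 0.09, 0.4² = 0.16, 0.5² = 0.25 and 0.6² = 0.36.

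**Step 2: what reaches significance.** The critical value is |r| = t / √(n − 2 + t²), with t the 97.5% point on n − 2 degrees of freedom: 0.444 at n = 20 and 0.254 at n = 60.

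**Step 3: how often the plain coefficient is significant.** By Fisher's z, atanh(r) × √(n − 3) is compared with 1.96. For r = 0.25:
- n = 60: 0.2554 × √57 = 1.93, so P(Z > 1.96 − 1.93) ≈ 49%.
- n = 20: 0.2554 × √17 = 1.05, so P(Z > 1.96 − 1.05) ≈ 18%.

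Simulation (40,000 trials per setting, normal or uniform age, no direct link) agrees. For Pearson:

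| Age correlation with both | Induced r | n = 20 | n = 60 | Age partialled out |
|---|---|---|---|---|
| 0.3 | 0.09 | about 7% | 10 to 11% | about 5% |
| 0.4 | 0.16 | 10% | 23% | about 5% |
| 0.5 | 0.25 | 19% | 49% | about 5% |
| 0.6 | 0.36 | 35% | 82 to 83% | about 5% |

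Spearman gives the same or slightly lower values (6.5, 10, 17 and 31% at n = 20 with normal age). The n = 60 column treats the patients as one sample. A group term, which the plan does not contain, hardly changes it (10, 22, 49 and 80%).

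**Step 4: where the effect shrinks (n = 20).**
- Unequal links: 0.5 with cognition and 0.2 with oxygenation gives an induced r of 0.10 and about 7% significant; 0.5 and 0.1 gives 0.05 and about 5.5%.
- Selection on cognition: groups are formed by MoCA, which narrows the cognitive range within a group. If a group is taken as the lower half of the score, age correlations of 0.3 to 0.6 give about 5 to 13% with uniform age, and up to 16% with normal age. This applies fully to MoCA and less to the other cognitive tests.

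**Step 5: the proposed method.** The partial correlation is (r_CO − r_AC × r_AO) / √[(1 − r_AC²)(1 − r_AO²)], where A is age, C cognition and O oxygenation, tested on n − 3 degrees of freedom. It is significant in about 5% of trials in every setting above, including those of Step 4.

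**The case against.** The strongest reply is that the Statistical analysis section names no variable pair, time point, or choice between levels and changes. The cognition-oxygenation pair is inferred from the aim. The Discussion (Expected research results) refers to possible changes in patients' profiles, so changes may be meant; if the age effect is constant over 12 weeks, correlating changes also gives about 5%. A condensed article may leave such detail to a fuller plan. This stands in part, and the point is therefore conditional on levels being used. But the article does state a method, and that method is unadjusted; adding age later would replace it.

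The size rests wholly on assumed correlations, and equal links are a favourable choice for the concern. The age limits are entry limits, not the spread that will be enrolled. This stands.

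Age is also not the only candidate: BMI (below 40) and AHI (15 or more) could be argued the same way. That is fair, but it does not make an unadjusted coefficient preferable, and age is known for every patient.

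A reader might infer that the tests fail to hold their 5% level. They do not: if both measures vary with age, the marginal correlation is truly non-zero and rejecting is correct. The error would lie in reading it as a direct link.

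**Conclusion.** The point holds as a matter of confounded interpretation. The only stated method for the relationship aim cannot separate a direct link between cognition and oxygenation from shared dependence on age, if levels at a visit are correlated.

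Its size is uncertain. With no direct link and age correlations of 0.3 to 0.6 with both measures, significance arises in about 10 to 83% of trials with 60 pooled patients and about 7 to 35% with one group of 20. Within a group it can be close to 5% when the oxygenation link is weak, and about 5 to 13% when patients were selected on the cognitive score under uniform age.

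Two stronger readings might be inferred and are not supported. One is that a spurious result inside a single group is likely; it is possible, but the inflation is small across much of the plausible range. The other is that the trial's treatment effect is biased; the A versus B comparison is randomised and does not rest on these correlations.

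**What to change.** In Statistical analysis, state that the cognition-oxygenation relationship will be assessed by partial correlation (Pearson or rank) adjusted for age, and name the time point. Label any unadjusted correlation of levels as descriptive.

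The cost is one sentence and one degree of freedom. No new data are needed, since age is an entry criterion.

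Correlating 12-week changes is an optional complement. It removes stable patient characteristics and sits closer to the question about exercise, but change scores are noisier, and they remove the age effect only if it is constant over the 12 weeks. Both steps together are not required.

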## Discussion

This study is designed to explore the impact of a 12-week tele-exercising program on the cognitive profile as well as on specific parameters of brain function and sleep architecture in OSA patients without CPAP treatment. In addition, this study aims to highlight the multidimensional relationship between physical exercise, cognition, brain oxygenation/metabolism, and sleep quality.

### Expected research results

In the context of our protocol, we will record and evaluate the effects of tele-exercising as a complementary treatment for OSA. Using a standardized assessment process at the clinical level and through exercise capacity tests, we will draw conclusions that will correlate with possible changes in the profiles of patients with OSA and related health indicators. At the same time, tele-exercising will empower patients to experience the benefits of physical activity, particularly structured exercise, fostering a healthier lifestyle, and ameliorating comorbidities related to sleep disorders. OSA is known to be a disease that is affected, among other things, by increased body mass and low physical activity which, in combination with the pathophysiology of the disease, leads patients to comorbidities. Poor sleep quality, as recorded through the multirecord sleep study, is highly correlated with cognitive decline in patients with OSA. Tele-exercising has been positively associated with reducing patients’ anxiety and depression, improving cardiopulmonary function, and enhancing quality of life. In addition, tele-exercising creates and develops skills due to the lack of supervision resulting in participants exercising for longer periods of time without being detrained.

